### **Importance of adherence**

Discussions on duration of use may be moot if adherence is not addressed. Pharmacotherapy adherence has been consistently linked to improved treatment outcomes, and adherence to the prescribed dose and treatment length is necessary to achieve maximum drug effect. Low adherence rates may lead to underestimates of the potential effectiveness of NRT. When smokers who are trying to quit ‘slip’ and have a cigarette, they may feel that the NRT is not working and quit taking it. In reality, ‘slips’ while on NRT may be a sign that they should be raising the dose (e.g. using more nicotine gum). Our counseling in both arms of this study will specifically address ‘adherence support’ thereby increasing the validity of our study findings.

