| Adherence support counseling                                               | +   | ++     |
| Reduction in cigarette support                                             |     | ++     |
| NRT                                                                 |     |        |
| Combination therapy with patch & gum or lozenge                            | +   | +      |
| 12 weeks of therapy, contingent on quit date                               | +   |        |
| 52 weeks of therapy, all participants                                      |     | +      |
| + indicates that the topic is addressed                                    |     |        |
| ++ indicates that the topic is covered in more detail                      |     |        |

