
quit plan. The focus will then shift to increasing motivation to make another quit attempt, including confidence building, medication use, and cessation planning. The initial face-to-face session will last approximately 30 minutes and follow-up sessions will last on average 15 minutes. Rigorous attempts will be made to reach participants for all scheduled sessions with a minimum of 3 call attempts for each scheduled session including attempts during daytime and evening hours and on alternate days.

**NRT-SC.** Consistent with the current standard of care for smoking cessation, provision of NRT will be contingent upon the participant agreeing to set a quit date. If they can identify a quit date, they will receive a 10 week supply of NRT and will be instructed to start the NRT on their chosen quit date. The dose of NRT will be adjusted to the participants smoking history as outlined in Table 3. The dose of the NRT will follow conventional treatment guidelines and is consistent with the combined NRT treatment regimens that have been shown to be effective and safe in clinical trials. Participants using NRT will be provided with both verbal and written instructions on how to use the NRT and how to avoid and manage any potential side effects. Participants will be instructed to use the nicotine patch on a daily basis even if they slip and have a cigarette. Participants will be asked to anticipate times that they typically smoke and use the gum or lozenge before deciding if they should have a cigarette. Smokers will be asked to try to consume at least 6-12 doses of gum or lozenge each day depending on their current smoking history. At each counseling call, the counselor will conduct a telephone-based assessment of the quantity of NRT used and will use this information to try to help the participant maximize their adherence to NRT.

Table 3. Dosing guide for NRT

| Smoking history                      | Dose of NRT                                   |
|--------------------------------------|-----------------------------------------------|
| Patch                         |                                               |
| < 10 cpd                             | 14 mg patch                                   |
| 10-20 cpd                            | 21 mg patch                                   |
| 21 – 39 cpd                          | 35 mg (1-21 and 1-14 mg patch)                |

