All participants in the LT-NRT arm will be asked to begin their NRT immediately after the baseline visit using the same dosing schedule outlined in Table 3. They will receive a 3-month supply of NRT at baseline and an additional 3-month supply after the Month 3, 6 and 9 counseling sessions. (*The timing of the resupply of medications mimics the 3 month medication supply typically used in healthcare settings for other chronic diseases – thus enhancing the potential for generalizability and adoption of the proposed intervention.*) The baseline visit will focus on the use of NRT, NRT adherence, and how NRT can be used to support smoking reduction. Smokers interested in making a quit attempt will be given cessation advice and supportive counseling as described in the written support materials. LT-NRT participants who continue to smoke will be asked to continue their NRT regardless of their current level of smoking and will be given supportive advice on maximizing adherence with NRT. LT-NRT participants who have quit smoking will be asked to continue NRT for a minimum of 6 months after they no longer experience smoking-related urges. If they have been abstinent for 6 months and no longer have urges to smoke, they will be provided a regimen for tapering their NRT dose with strict instructions for resuming the full dose if they have a slip or if smoking-related urges recur. LT-NRT participants will also receive adherence support counseling. Since some of the LT-NRT participants will not be ready for extensive counseling on quitting, the adherence support counseling will be particularly important. Adherence support counseling has been previously tested by our group and will assist participants in identifying problems remembering to take their medication and help them develop strategies for remembering (e.g., timing doses with routine activities of daily living, posting reminders, setting alarms). Adherence support counseling will reinforce the continued use of NRT as one of the single best strategies for quitting or reducing smoking. This counseling will follow a semi-structured format that assesses smoking status and medication use, probes for difficulties participants are having with their medication, assists participants in problem-solving around issues they are having remembering to take their medications, and offers suggestions for dealing with self-reported side effects. Notably this counseling approach has resulted in high rates of adherence to smoking cessation medication (86%, biochemically verified). In the present study, we will not be able to biochemically verify adherence to NRT since nicotine in the blood could reflect either adherence to the treatment or continued smoking. Instead, adherence will be assessed using a 3-day recall of medication use. This approach is considered the gold standard when biochemical verification of adherence is not possible and in our own work has been validated with high sensitivity and specificity against medication blood levels.

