| Nicotine dependence          | Fagerström Test for Nicotine Dependence (FTND) ,  time to first cigarette (baseline, Mo 12); Brief WISDM  among continued smokers at month 12. |
| Nicotine intake              | Urinary cotinine/creatinine ratio (baseline, Mo 3, 6, and 12)                                                                                                                    |
| Clinical Variables           |                                                                                                                                                                                  |
| Respiratory function         | FEV1 (baseline)                                                                                                                                                                  |
| COPD symptoms                | CAT score, # of hospitalizations for COPD in past year (baseline)                                                                                                                |
| Treatment Variables          |                                                                                                                                                                                  |
| Medication adherence         | 3-day medication use recall (Mo 3, 6, and 12)                                                                                                                                    |
| Counseling adherence         | total counseling sessions completed                                                                                                                                              |

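### The NRT adherence recall in Table 5 (months 3, 6 and 12) is mistimed for the SSC arm: supply has ended by months 6 and 12, and often by month 3

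*Protocol*

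**What the plan says.** **The measure.** Under Treatment Variables, Table 5 (Covariates) has one row for medication adherence: "3-day medication use recall (Mo 3, 6, and 12". The LT-NRT intervention section explains the choice. Nicotine in blood may come from smoking or from treatment, so biochemical checking is ruled out: "Instead, adherence will be assessed using a 3-day recall of medication use".

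**SSC supply.** The NRT-SC paragraph says that participants who can name a quit date "they will receive a 10 week supply of NRT and will be instructed to start the NRT on their chosen quit date". Study design and Intervention also say 10 weeks. Table 2 says "12 weeks of therapy, contingent on quit date". Follow-up calls at weeks 1, 3, 6 and 10 go to those interested in quitting within 30 days. Someone not ready at baseline can still join the SSC counselling protocol during the first 6 weeks.

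**LT-NRT supply.** All participants start immediately after baseline and have 52 weeks.

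**Other questions about NRT use.** In SSC, "At each counseling call, the counselor will conduct a telephone-based assessment of the quantity of NRT used", and the stated purpose is to help the participant adhere. LT-NRT counselling also asks about medication use, at weeks 1, 3 and 6 and months 3, 6 and 9. Table 5 lists neither.

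**The concern.** A 3-day recall records use over the three days before it is asked. It can measure adherence only while the participant should be on treatment. In LT-NRT all three readings fall within the supply year. In SSC at least two of the three fall after supply has ended, when the recall can pick up only leftover or self-bought product. One variable then means two different things in the two arms.

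The protocol itself gives adherence weight. Its section on the subject warns that "Low adherence rates may lead to underestimates of the potential effectiveness of NRT" and says that adherence support in both arms makes the findings more valid. A reader who asks whether the control course was taken as assigned should be able to find the answer in the named adherence variable.

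Nothing else in Table 5 fills the gap. Urinary cotinine cannot separate NRT from smoking, counselling adherence counts sessions, and use of other nicotine products including NRT is recorded at baseline only. The dates on which data are collected cannot be changed later in an analysis plan.

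**Working it through.** The protocol gives no figure for how far the recall overlaps SSC supply, so there is none to reproduce on this point. Its sample size does reproduce: 10% against 20%, two-sided 5%, 80% power and pooled variance give 199 per arm. That figure does not depend on adherence.

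**Inputs**
- Recall at months 3, 6 and 12 (Table 5).
- SSC supply of 70 days (NRT-SC) or 84 days (Table 2), starting on quit day *d*.
- Quit day between 0 and 30. The 30-day limit comes from Counseling-SSC. An even spread over those 31 days is an assumption, because the protocol gives no distribution.
- Month 3 taken as about day 91, so the recall covers days 88 to 90. Month 6 taken as about day 183.

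**Month 3.** A supply of *S* days covers days *d* to *d* + *S* − 1.
- All three recall days are covered if *d* + *S* − 1 ≥ 90.
- At least one is covered if *d* + *S* − 1 ≥ 88.

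| Supply | Fully covered | Any overlap | Wholly missed | Not fully covered |
|---|---|---|---|---|
| 70 days | *d* ≥ 21: 10/31 = 32% | *d* ≥ 19: 12/31 = 39% | 19/31 = 61% | 21/31 = 68% |
| 84 days | *d* ≥ 7: 24/31 = 77% | *d* ≥ 5: 26/31 = 84% | 5/31 = 16% | 7/31 = 23% |

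With 10 weeks, a quit date on day 0, 7 or 14 ends supply on day 70, 77 or 84. That is 21, 14 or 7 days before month 3.

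**Months 6 and 12.** Take the latest plausible start: entry at week 6 (day 42) plus a further 30 days to the quit date (assumption), which is day 72. Supply then ends on day 72 + 70 = 142 (about week 20) or 72 + 84 = 156 (about week 22). The second is still 183 − 156 = 27 days before month 6. Both later readings miss supply under either duration.

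**Existing SSC calls.** Count the weeks from baseline and use the same 3-day window before each call.
- Week 6 covers days 39 to 41 and week 10 covers days 67 to 69. Both lie wholly within a 70-day supply for every *d* from 0 to 30, since *d* ≤ 39 and *d* + 69 ≥ 69.
- Week 3 covers days 18 to 20 and lies within supply if *d* ≤ 18, which is 19/31 = 61%. These are the same participants whose month-3 recall is wholly missed with a 10-week supply.
- Week 1 covers days 4 to 6 and lies within supply only if *d* ≤ 4.

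So a completed schedule of calls gives every such participant at least two on-treatment readings, where Table 5 gives most of them none under the 10-week figure.

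**The case against.** The case on the other side is substantial, and much of it stands.

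- **Other measurement exists.** A reader might infer that SSC use is measured only at months 3, 6 and 12, or that the trial cannot show that the control course was taken. The documents do not support this, because NRT quantity is assessed at every SSC call. What is missing is any statement that those answers are study data.
- **Recorded use is not bound to be near zero.** That reading fails at month 3, where 32% to 39% of quit dates leave supply running with 10 weeks and 77% to 84% with 12. Late entry, leftovers and self-bought NRT can also give non-zero values.
- **The size rests on an assumption.** The spread of quit dates is not documented, and the conflict between 10 and 12 weeks largely decides how much is lost at month 3. It does not rescue months 6 and 12.
- **No stated analysis uses adherence.** The Aim 1 primary test compares abstinence by intention to treat. The Aim 2 candidates are demographic, psychosocial, biological and smoking factors, and Table 5 lists treatment variables separately. No rule codes a participant who finished the course as a non-user, so biased efficacy cannot be inferred.
- **The recall has a proper use.** It records current NRT use at the visits where CO, NNAL and cotinine are measured, and being off supply late in the year is the assigned contrast in SSC. This is a reason to keep it under an accurate label.

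How adherence is derived may be left to an analysis plan. That does not settle whether the counselling answers are collected as study data in a usable format.

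**Conclusion.** The adherence variable named in the protocol is mistimed for SSC. Months 6 and 12 fall after supply under both stated durations, provided that entry is limited to the first 6 weeks and the quit date follows within about 30 days. At month 3 the recall wholly misses supply for about 61% of fully adherent SSC users with 10 weeks (68% not fully covered), or about 16% (23%) with 12, given evenly spread quit dates.

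In SSC it therefore measures current NRT use at outcome visits. A between-arm comparison of it as adherence would largely reflect timing. The damage is limited to describing delivery of the control treatment and to any exploratory use of adherence. The primary comparison and the sample size are untouched. The change should be made, but the trial's main conclusion does not depend on it.

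**What to change.** 1. In Table 5, name NRT use recorded in the 3-day format at existing contacts as the on-treatment adherence data: weeks 1, 3, 6 and 10 for SSC; weeks 1, 3 and 6 and months 3, 6 and 9 for LT-NRT. Add the month-12 assessment visit for LT-NRT, which has no counselling session then.
2. Define adherence relative to each participant's NRT start date and supply window, and do not count SSC calls made before the quit date.
3. Keep the SSC recall at months 3, 6 and 12, labelled as current NRT use, and as use outside the assigned course once supply has ended.
4. Reconcile the 10 weeks in the text with the 12 weeks in Table 2, since the supply window depends on it.

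The cost is one table row and a short structured form at contacts that already ask about NRT. Treatment, visits and sample size do not change. There are three downsides. The data are collected by the counsellors who coach adherence, not by the research assistants. They are missing for participants who are not reached. They do not exist for SSC participants who set no quit date, who should be reported as not dispensed.

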### Analytical Plan.

**Sample Size and Power Calculations.** Our sample size was based on our primary outcome, point-prevalence abstinence at Month 12, using an intent-to-treat approach. Based on prior studies using precessation NRT, we estimate a 2-fold increase in cessation outcomes in the LT-NRT group compared to the SSC group. Given our recruitment of patients at all levels of readiness to quit, we estimate a 12 month cessation rate of 10%. With 199 participants, in each arm, we will have an 80% power to detect a 2-fold difference or greater with a Type I error rate of 5%. This sample size will provide comparable power for looking at 6 month sustained cessation. For the CO measured longitudinally at four time points, we have 80% power to detect a mean difference of 2.24 ppm. Likewise, for NNAL, we have 80% power to detect a mean difference of 0.41 pmol/mg creatinine or more between the two groups.

**Specific Aim 1: Compare the benefits of traditional smoking cessation (SSC) versus long-term guided maintenance therapy (LT-NRT) with NRT.** The chi-square test will be used to compare the verified 7-day point prevalence abstinence at Month 12 between the two groups. If there is imbalance between treatment groups at baseline, we will switch to logistic regression for our primary analysis. We will use similar methods to test for group differences for dichotomous secondary outcomes including sustained abstinence and proportion with 1 or more ED visits or hospitalizations. To test for differences in change in respiratory symptoms and FEV1 from baseline measured at 3, 6, and 12 months, we will use standard mixed models repeated measures analysis. Likewise, to test for differences in longitudinal exposure to CO and NNAL, we will compare the area under the curve over the entire 12 months of follow-up using repeated measures analysis. If the treatment differences are heterogeneous across any covariate sub-groups, we will quantify and report such interactions

with appropriate contrast statements. We will compare the cumulative number of self-reported quit attempts by means of a Wilcoxon rank-sum test.

As smoking cessation trials are likely to have missing data, we will adopt the approach of Hedeker et al. for analyzing the primary binary outcome of smoking abstinence. We will initially conduct our analyses ignoring missing data and then conduct sensitivity analysis using three different approaches. The first approach will impute data under the two extreme assumptions of ‘missing = smoking’ and ‘missing = non-smoking’. The second approach will impute data using the last observation carried forward method, and finally we will conduct multiple imputations for missing data, modeling the uncertainty inherent in individual patient outcomes using a logistic regression model.

**Specific Aim 2: Develop estimates of patient-desired outcomes based on patient-specific characteristics and treatment choice (SSC vs. LT-NRT)** We will employ a Classification and Regression Tree (CART) analysis to identify subgroups of participants whose personal characteristics might impact the benefit of treatment. The resulting decision tree will allow smokers and their care providers to estimate their individual chances of success given their choice of treatment. To maximize the utility of the decision tree, we will start by soliciting input from our Stakeholder Advisory Committee and Patient Advisory Panel. We will ask them to identify key demographic, psychosocial, biological, and smoking factors from Table 5 and help us convert them into clinically meaningful binary variables that could be tested for inclusion in a clinically meaningful decision tree. (Drs [name] and [name] will provide both groups with simple conceptual models to assist them in providing meaningful, independent contributions.) The candidate variables, along with treatment assignment (LT-NRT vs SC) will be entered into a recursive partitioning model as described by Brieman and Friedman using the RPART package in the R statistical software. Specific methods related to building the tree (using appropriate splitting criteria and loss incorporation using the altered priors method), pruning the tree and handling missing data (using surrogate variables) will be deployed using the techniques described by Therneau et al. Given the event rates expected and overall sample size, a validation subsampling scheme will not be feasible, thus we will utilize 10-fold cross-validation on the regression tree to assess its properties. Additionally, we will account for the uncertainty in tree classification by generating a bootstrap sampling distribution of the CART as described by Shalizi. In addition to developing a CART model/decision tree for smoking cessation, separate classification models will be developed for other high priority binary outcomes, including: 1) 6 month sustained abstinence; 2) 50% reduction in carcinogen (NNAL) exposure; and 3) COPD related hospitalization (yes/no). (These were the models of greatest interest for our initial Patient Advisory Panel, but other outcomes could be modeled as well if our patients and stakeholders think that these additional models might be useful.)

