### **Intervention – Long-term Guided Maintenance Therapy (LT-NRT) arm**

**Written materials-LT-NRT.** LT-NRT participants will receive the same written materials as those provided to SSC participants. This will include information on the benefits of quitting smoking and the importance of home smoking restrictions. Although the materials are identical, the smoking plan page that will be utilized in counseling and the instructions for completing it will be tailored to fit the arm, with participants in the LT-NRT group being instructed to start NRT immediately and continue its use longer term. They will receive the same information on use of combination NRT (patch plus gum or lozenge) and troubleshooting suggestions if they experience adverse symptoms from the NRT. Tips on medication adherence will be modified to address the long term nature of the treatment. As with the SSC arm, the materials will be available in either English or Spanish and will provide a number that the participants can call 24/7 if they believe they are having problems related to their treatment.

**Long-term Guided Maintenance Therapy (LT-NRT).** For the LT-NRT recipients, the counseling and NRT are integrally linked. While standard smoking cessation approaches (including our SSC comparison) address smoking cessation as a ‘one-time event’, our LT-NRT approach addresses smoking as a chronic disease that requires long term treatment. Indeed, our LT-NRT approach borrows heavily from the chronic care model of disease management and mimics techniques of patient activation and medication management used in treatment of other chronic illnesses such as diabetes and hypertension. Accordingly, our LT-NRT empowers patients with the skills to manage their NRT, reduce their cigarette consumption, and prepare themselves for quit attempts as they become ready.

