| 6 month sustained smoking abstinence               | Self reported 6 month abstinence at 12 month confirmed by exhaled CO or proxy validation (Mo 6 & 12)                                                                                                                                                                 |
| Quit attempts                                      | Cumulative number of self-reported quit attempts lasting at least 24 hours (baseline, Mo 3, 6 & 12)                                                                                                                                                                  |
| Average CPD                                        | Average number of CPD (baseline, Mo 3, 6 & 12)                                                                                                                                                                                                                       |
| Smoke exposure                                     |                                                                                                                                                                                                                                                                      |
| Cumulative CO exposure over 12 months              | Expired CO will be measured at each follow-up visit allowing an assessment of cumulative CO exposure. (baseline, Mo 3, 6 & 12)                                                                                                                                       |
| NNAL exposure over 12 months                       | Urinary NNAL will be measured at each follow-up visit allowing an assessment of cumulative NNAL exposure. (baseline, Mo 3, 6 & 12)                                                                                                                                   |
| Clinical outcomes                                  |                                                                                                                                                                                                                                                                      |

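### The claim of comparable power for 6-month sustained abstinence does not hold under the protocol's own 2-fold assumption

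*Protocol*

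**What the plan says.** In the protocol's Analytical Plan, the paragraph on sample size and power states a base rate ("we estimate a 12 month cessation rate of 10" per cent) and an effect ("we estimate a 2-fold increase in cessation outcomes in the LT-NRT group compared to the SSC group"). It continues "With 199 participants, in each arm", and concludes "we will have an 80% power to detect a 2-fold difference or greater", at a 5% Type I error. The next sentence is "This sample size will provide comparable power for looking at 6 month sustained cessation". No sustained rate, effect or calculation accompanies it.

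The Measures section defines the primary outcome as verified abstinence over the last seven days at month 12. Table 4 defines the sustained outcome as "Self reported 6 month abstinence at 12 month confirmed by exhaled CO or proxy validation (Mo 6 & 12"). Under Specific Aim 1, sustained abstinence is to be tested by methods similar to the chi-square test used for the primary.

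**The concern.** The two outcomes are nested. Six months without smoking, verified at month 12, implies seven days without smoking at the same visit. Someone who quits, or slips and quits again, after month 6 can count for the primary outcome but not for the sustained one. The LT-NRT arm allows for late quitting: participants are to "prepare themselves for quit attempts as they become ready", with counselling continuing at months 6 and 9.

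At a fixed risk ratio, a lower event rate means lower power. If the primary comparison has just 80%, a rarer outcome with the same ratio has less.

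Sustained abstinence is the first secondary outcome listed and is one of the outcomes for which a separate classification tree is planned. A reader who takes the sentence at face value would believe that a non-significant result came from a comparison with roughly 80% power.

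**Working it through.** **Inputs from the protocol (Analytical Plan).** 199 per arm; 5% Type I error, taken as two-sided; base rate 10%, taken as the SSC rate; ratio 2; chi-square test. The protocol does not state the sidedness or name the arm for the 10%, but this reading reproduces its sample size.

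**Formula** (pooled variance under the null, no continuity correction), with d = p2 − p1 and p̄ = (p1 + p2)/2:

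Power = Φ{ [d√n − 1.96·√(2p̄(1 − p̄))] / √(p1(1 − p1) + p2(1 − p2)) }

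**Step 1: reproduce the stated figure.** For 10% v 20%, n = 199: d√n = 0.10 × 14.107 = 1.4107; 1.96 × √(2 × 0.15 × 0.85) = 0.9897; √(0.09 + 0.16) = 0.5000. Then (1.4107 − 0.9897)/0.5000 = 0.842 and Φ(0.842) = 80.0%. Solving for n gives 198.96, that is, 199. The stated figure is correct and leaves no margin.

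**Step 2: the bound on the sustained rate.** By the definitions, sustained rate ≤ month-12 rate in each arm. Under the planning values this means at most 10% in SSC and at most 20% in LT-NRT. Equality in an arm requires that every month-12 abstainer there had already been abstinent for six months.

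**Step 3: power at lower rates, ratio kept at 2.** The documents give no sustained rate, so a range is assumed. Example, 8% v 16%: d√n = 1.1285; 1.96 × √(2 × 0.12 × 0.88) = 0.9007; √(0.0736 + 0.1344) = 0.4561. Then 0.2278/0.4561 = 0.499 and Φ(0.499) = 69.1%.

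| SSC v LT-NRT (assumed) | Share of month-12 abstainers who are sustained | Power at 199 per arm | n per arm for 80% |
|---|---|---|---|
| 10% v 20% | 100% | 80.0% | 199 |
| 9% v 18% | 90% | 75.0% | 226 |
| 8% v 16% | 80% | 69.1% | 258 |
| 7% v 14% | 70% | 62.6% | 300 |
| 6% v 12% | 60% | 55.3% | 356 |
| 5% v 10% | 50% | 47.3% | 435 |

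Exact enumeration of the chi-square test gives 80.9% at 10% v 20%, 69.6% at 8% v 16%, 55.7% at 6% v 12% and 48.1% at 5% v 10%, so the approximation does not drive the result.

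**Step 4: how much slack there is.** At ratio 2, power stays within two points of 80% only if the SSC sustained rate is at least about 9.6%, that is, if about 96% of month-12 abstainers are also sustained abstainers.

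**Step 5: the ratio that would rescue the claim.** For 80% power at 199 per arm, the ratio must be about 2.16 at an SSC rate of 8% (17.3% in LT-NRT), 2.42 at 6% (14.5%) and 2.60 at 5% (13.0%). The protocol assumes none above 2.

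**The case against.** The strongest reply is that power depends on both rates, so nesting alone does not lower it. That is correct. With the same formula and 199 per arm, 9% v 19% gives 82%, 8% v 18% gives 85% and 7% v 16% gives 81%, all within the 10% and 20% bounds. A reader might infer that 80% is attainable only if nobody quit after month 6. That is false, because the loss also requires that the ratio stay near 2 or fall.

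A reader might also infer that late quitting in LT-NRT must shrink the ratio. The documents do not settle this. LT-NRT supplies NRT for 52 weeks and asks quitters to stay on it, whereas the SSC supply is 10 weeks (12 in Table 2). Better maintenance could raise the ratio for sustained abstinence, just as late quitting could lower it.

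Nor does nesting prove a strictly lower sustained rate. It proves lower or equal.

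Finally, comparable is a loose word and might cover 75%. It does not reasonably cover 47% to 69%, and without a stated rate nobody can tell which applies.

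What remains is that the protocol's single stated effect is a 2-fold increase in cessation outcomes generally. Under that effect, the sentence holds only if almost every month-12 abstainer is also a sustained abstainer. This is an affirmative claim, so it is not a detail left for a statistical analysis plan.

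**Conclusion.** Wrong as written; minor to moderate. Under the protocol's 2-fold assumption, power for sustained abstinence is below 80% for any SSC rate under 10%: about 75% at 9%, 69% at 8%, 55% at 6% and 47% at 5%. The direction rests on two things: the ratio staying at 2, as the protocol assumes, and some abstainers at month 12 having quit or re-quit after month 6, which a gradual-quitting design leads one to expect. The size of the loss rests on assumed rates.

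A reader might go further and conclude that the trial is undersized. The documents do not support that. The sample size was expressly set on the primary outcome, and 199 per arm reproduces exactly. No test or analysis method is affected.

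**What to change.** Delete the sentence, or replace it with the sponsor's expected sustained rate in each arm and the power that follows at 199 per arm. If a ratio other than 2 is expected, state it and give its basis. In either case, note that at a 2-fold ratio power is below 80% for any SSC rate under 10%, for example 69% at 8% v 16% and 47% at 5% v 10%, and mark those rates as illustrative.

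The cost is one sentence and a less favourable stated figure. The sample size, the primary analysis and the conduct of the trial do not change.
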